### 6.4 Sample Size and Power

In health facilities where there are  $< 50$  HIV-infected pregnant or postpartum women in the baseline or endline cohorts (determined with the ANC register), we will abstract data from the ART register on all women. At health facilities where there are  $\geq 50$  HIV-infected pregnant or postpartum women in the cohorts, we will abstract a predetermined sampling fraction such that 75% of women are sampled from cohorts with 50-100 women, 50% of women are sampled from cohorts with 100-200 women, etc. This approach will ensure that the sample size is adequate to detect a minimum increase in retention in care at 90 days postpartum.

We have powered the study for the outcome of retention in care 90 days postpartum. In our aforementioned preliminary analysis of pregnant women in Shinyanga, we found that more than

36% of HIV-infected pregnant women who initiated ART were lost within 100 days. Thus, we will conservatively assume that in the comparison communities, 67% of women will be retained in care at 90 days postpartum. For logistical and budgetary reasons, especially given the rapid nature of the impact evaluation, we have determined that we can reasonably study 15 intervention communities (a total of 30 CHW, 2 per village, and 15 RCH facilities) and 15 comparison communities.

If we assume an ICC of 0.05 and that the intervention will increase the proportion of women who are retained in care 90 days postpartum from 67% to 80% (detectable effect size of 13 percentage points, or 20%), we will require at least 36 observations per community, or 537 observations from the intervention and comparison groups, to have 80% power to reject the null hypothesis of no effect. Obtaining data from at least 36 HIV-infected women per facility is well within the normal volume of clients at RCH clinics, as many RCH clinics initiate an average of 11 HIV-infected women on ART/ARVs per month. With at least 6 intervention months in each community, we will ensure that we can easily meet this goal.

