All three indicators will be measured primarily from ANC records, though we will also back check these records with CHW logs to ensure accuracy and quality of the data. We will analyze all three measures through difference in difference strategy in order to capture differences in outcome between the control and treatment groups.

**7.5. Evaluation Question #2:** Is the impact of integrating community-based MNCH and PMTCT

*services on retention in care and adherence greater among women who had more contact with CHWs?*

To answer this question, we will monitor the CHW logs to measure (a) the duration of visits with CHWs and (b) the frequency of visits (per week, per month). We will then compare the frequency and duration of visits to each woman's retention in the program, and their level of participation (measured through adherence to ART) to find the correlation between CHW contact and participation.

*7.6. Evaluation Question #3: Is integration of community-based MNCH and PMTCT services acceptable and feasible for CHW, health facility staff, and pregnant and postpartum women, and are there potential spillover benefits on other maternal health outcomes?*

We will conduct a mixed methods process evaluation, including quantitative analysis of process outcomes feedback from stakeholders (two facility personnel, five CHWs, five clients, two Amref staff), and in-depth interviews with women, in order to better understand the effectiveness and feasibility of the intervention. We will focus our efforts on answering the following key questions:

- a. Was the intervention implemented as intended? Was there heterogeneity in implementation? Were standard operating protocols followed consistently and correctly?
- b. Were there community- or facility-level factors that influenced the success of the intervention? Was the intervention impeded by the time availability of CHW or facility staff?
- c. Did the intervention motivate pregnant and postpartum women? How? What aspects were motivating and why? Did the intervention inadvertently increase stigma?
- d. What were successful or challenging aspects of the intervention throughout the causal chain (**Figure 1**)? What could be improved?

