## 9. LIMITATIONS

As with any study design, ours is not without limitations. Because the control and treatment groups will be measured at different times, time may be a confounding factor to the analysis and a threat to internal validity. We minimize this effect, however, by measuring information about the women at a similar point in time in their pregnancy (90 days postpartum). We do not anticipate significant issues in validity due to the time period of data collection.

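### The 80% power in 6.4 is for a single-period two-arm comparison, not the difference-in-differences fixed in 7.4; adjusting endline for the cluster's baseline is never less precise, apart from one degree of freedom, and uses the same data

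*Protocol*

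**What the plan says.** Section 7.4 names one estimator for timing of ART initiation, retention and adherence: "We will analyze all three measures through difference in difference strategy in order to capture differences in outcome between the control and treatment groups".

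Section 6.3 randomises 30 villages and measures them at baseline and at endline. Section 7.1 defines the two cohorts by birth window, April to September 2014 and February to July 2015. They are essentially different women from the same villages.

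Section 6.4 sizes the study on one outcome: "We have powered the study for the outcome of retention in care 90 days postpartum". Its inputs are 67% against 80% retained, 15 communities per arm, and an intracluster correlation ("If we assume an ICC of 0.05"). It asks for at least 36 observations per community, or 537, "to have 80% power to reject the null hypothesis of no effect". It mentions neither a baseline period in the variance nor a correlation between periods.

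Section 9 says: "Because the control and treatment groups will be measured at different times, time may be a confounding factor to the analysis".

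**The concern.** A power statement should describe the analysis that will be run. Differencing brings in the sampling error of the baseline cohort and removes only the part of the cluster effect that persists to endline. Whether the net variance is higher or lower than that of an endline comparison depends on how stable the clusters are. Section 6.4 takes no account of either effect.

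Differencing is also not needed here to remove bias, because the villages are randomised. The same baseline data can be used as a covariate, which extracts at least as much precision. With the number of communities set by logistics and budget (6.4), the choice of analysis is the cheapest source of power left. At stake is the chance of detecting the 13-point gain in retention for which the study was sized.

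**Working it through.** **Inputs from the protocol.** 67% and 80% retained; ICC 0.05; k = 15 communities per arm; m = 36 per community; power 80% (all 6.4). Different women in the same villages in two periods (6.3, 7.1).

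**Assumptions.** Two-sided alpha of 0.05, which 6.4 does not state but which reproduces its figure. The cluster autocorrelation (CAC), the correlation of a village's true level between the two periods, is not in the protocol and is run from 0 to 1. The same m applies in each period.

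**Step 1: reproduce the stated sample size.**
- Two proportions, 67% vs 80%, pooled variance: n = 179.7 per arm.
- With continuity correction, (n/4)·[1 + √(1 + 4/(0.13n))]² = 194.8, so 195.
- Design effect: 1 + 35 × 0.05 = 2.75.
- 195 × 2.75 = 536.25, so 537 per arm; 537/15 = 35.8, so 36 per community.
- Without the continuity correction, 180 × 2.75 = 495, which does not match.

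The stated figure is thus a one-period, two-arm calculation, and 537 is a per-arm number.

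**Step 2: variance of each analysis relative to endline-only.** The correlation of a cluster's baseline and endline means is

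r = CAC × m·ICC / [1 + (m−1)·ICC] = CAC × 1.8/2.75 = 0.6545 × CAC.

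- Difference-in-differences: 2(1−r)
- Endline adjusted for cluster baseline: 1−r²
- Gap: 2(1−r) − (1−r²) = (1−r)², never negative
- Adjusted as a fraction of differencing: (1+r)/2

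**Step 3: power at 36 per cluster.** The endline-only standard error is √[(0.67×0.33 + 0.80×0.20) × 2.75/(15×36)] = 0.0441. Power is from the noncentral t with 28 degrees of freedom (27 for adjusted). Endline-only power is 81%.

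| CAC | r | Variance, differencing | Variance, adjusted | Power, differencing | Power, adjusted |
|---|---|---|---|---|---|
| 0 | 0 | 2.00 | 1.00 | 52% | 81% |
| 0.5 | 0.33 | 1.35 | 0.89 | 69% | 85% |
| 0.7 | 0.46 | 1.08 | 0.79 | 78% | 89% |
| 0.8 | 0.52 | 0.95 | 0.73 | 83% | 92% |
| 1.0 | 0.65 | 0.69 | 0.57 | 93% | 96% |

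A beta-binomial simulation with t tests on cluster means gives the same ordering. Differencing against adjusted is 50% vs 81% at CAC 0, 66% vs 84% at 0.5, 80% vs 90% at 0.8 and 91% vs 96% at 1.

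**Step 4: the CAC below which differencing misses 80%.**
- m = 36: about 0.74. If the baseline binomial variance is taken at 67% in both arms, as 6.4's own assumption implies, it is about 0.80.
- m = 50: about 0.59.
- m = 66: about 0.50.

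The larger sizes come from 6.4. An average of 11 initiations a month over 6 months is 66 women, and the 75% sampling fraction for cohorts of 50 to 100 gives 0.75 × 66 ≈ 50.

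**Step 5: Section 9 against 6.3 and 7.1.** Both arms are measured in the same baseline window and the same endline window. The cohorts differ in time; the arms do not.

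**The case against.** The strongest objection is that the power loss turns on a CAC that the protocol does not give. The same villages and facilities are measured in birth windows ten months apart, so a high CAC cannot be ruled out. At CAC 0.8 to 1, differencing has 83% to 93% power and does better than endline-only. In addition, 36 is a minimum: on the clinic volumes in 6.4 many clusters could supply 50 to 66 women, which lowers the threshold to 0.59 or 0.50. This stands, although 6.4 says that many clinics reach that volume, not all.

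Four stronger readings are tempting, and the document does not support them.
- A reader might infer that the trial will be underpowered. It may be, depending on CAC and cluster size.
- A reader might put the lost precision at a flat quarter to a third. From (1+r)/2, adjustment has 34% less variance than differencing at CAC 0.5 and 24% less at 0.8, but 17% less at CAC 1.
- A reader might take differencing to be invalid. Under randomisation it is unbiased, only less efficient.
- A reader might take Section 9 as the rationale for differencing. It never mentions differencing; the stated purpose is in 7.4. Its misstatement about timing is a separate wording error.

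It can also be said that model details belong in a statistical analysis plan. That is true of the model form and the degrees of freedom. But the protocol itself names the estimator and claims a power, and the two do not match.

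**Conclusion.** Two things hold whatever the CAC. First, the 80% in 6.4 was calculated for an analysis that 7.4 does not plan. Second, adjusting the endline comparison for the cluster's baseline is never less precise than differencing, apart from one degree of freedom (27 against 28), which is negligible with 30 clusters.

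The shortfall in power is conditional. At ICC 0.05 and 36 per cluster, differencing has between 52% and 93% power over the full CAC range, against 81% to 96% for the adjusted analysis. These figures assume two-sided alpha 0.05, equal cluster sizes in both periods and, in the table, equal variances at baseline and endline.

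The Section 9 sentence is wrong as written, and it concedes a confounding threat between arms that concurrent randomised controls remove.

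**What to change.** - **7.4:** make the primary analysis the endline comparison between randomised arms, adjusted for each cluster's baseline value of the same outcome and accounting for clustering. Keep difference-in-differences as a sensitivity analysis.
- **6.4:** state that the 80% applies to an endline comparison, or restate power for the chosen analysis over an explicit range of CAC. State that 537 is per arm.
- **Section 9:** say that the baseline and endline cohorts, not the control and treatment groups, are measured at different times.

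The cost is protocol wording and a short recalculation. No further data are needed, because the baseline cohort is already to be collected.

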## **8. ETHICAL CONSIDERATIONS**

This evaluation has been approved by ethical review boards at the University of California, Berkeley, conditional on approval by the Amref Health Africa Tanzania review board.

A primary concern the study team has faced has been to ensure the data collection maintains the anonymity of patients. In order to ensure this in the quantitative of the study, we will abstract medical record information from randomly sampled women. Information will come from medical and pharmacy records, and CHW logs. We will identify patients by their ANC ID number in order to pool data from these various sources. Once merged, we will drop identifying information (clinic ID, birthdate). Other demographic information will be retained (age in years,

ethnicity, education, etc.), but none of these variables will be identifiable without the clinic ID or birthdate.

In the qualitative evaluation, we will only collect basic demographic information in order to ensure diversity in the study population (e.g., sex, age in years, year of HIV diagnosis and year of ART initiation, if applicable). Interviews will be audio recorded, and the audio files and transcripts will be identified with a number only for record keeping purposes. The number will not be used to link particular findings back to an individual participant. Audio files, once transcribed, will be securely stored and later destroyed (one year after the study's conclusion).

## 9. LIMITATIONS

As with any study design, ours is not without limitations. Because the control and treatment groups will be measured at different times, time may be a confounding factor to the analysis and a threat to internal validity. We minimize this effect, however, by measuring information about the women at a similar point in time in their pregnancy (90 days postpartum). We do not anticipate significant issues in validity due to the time period of data collection.

## 10. ABBREVIATIONS

ANC = Antenatal care

ART = Antiretroviral therapy

ARV = Antiretrovirals

CHW = community health worker

eMTCT = elimination of mother-to-child transmission

MNCH = maternal, newborn and child health services

PMTCT = Prevention of mother to child transmission

RCH = Reproductive and child health

